## Abstract

Background: Patients with scoliosis often require multiple imaging modalities. The aim of this study was to find out whether primary diagnosis, including surgical planning, could be carried out entirely without computed tomography (CT) scans and whether follow-up could be replaced with alternative methods without the use of X-rays. In order to reduce the radiation exposure in the diagnosis and treatment of severe scoliosis, we expect to replace X-rays with radiation-free or less-intensive radiation examinations. This study protocol is interdisciplinary. Methods: A total of 50 male and female patients (children and adolescents, aged 7–18 years) treated for scoliosis will be analyzed. In addition to routine projection radiographs, preoperative CT, and/or X-ray stereoradiography (EOS) examinations, thin-slice 3D magnetic resonance imaging (MRI) sequences will be retrospectively reformatted during the preoperative MRI examination. A three-dimensional back scan (video-raster stereography) and an intraoral scan will also be obtained. The following questions should be answered at the end of the project: (1) Can MRI examination with additional thin-slice 3D reconstruction answer all relevant questions for preoperative planning instead of CT? (2) Are EOS or whole-spine X-ray examinations in combination with MRI data sufficient for the evaluation of the pedicles and spinal deformity? (3) Does the Cobb angle in the radiograph correlate with the calculations from the back scanner image and can follow-up checks be replaced? (4) Are there any correlations between dental anomalies and scoliosis? Conclusions: Until now, pediatric patients with scoliosis have been diagnosed, monitored, and treated with numerous independent specialist disciplines, such as pediatricians, orthopedic surgeons, neurosurgeons, and general practitioners with different radiological issues. The aim of this project is to reduce radiation and lower perioperative risks by creating a preoperative and follow-up-related standard protocol in close interdisciplinary and targeted cooperation between all the specialist disciplines involved. In line with the holistic examination approach, the associated accompanying diseases and developmental disorders such as dental and neuronal malformations will also be examined. On the one hand, CT-based questions could be replaced with the reconstruction of thin-slice MRI sequences. In addition, it may be possible to use the three-dimensional back scan as an intermediate diagnostic procedure instead of X-rays in the monitoring of severe scoliosis. Insofar as correlations or causalities between scoliosis and occlusal anomalies, early orthodontic intervention could positively benefit the duration of therapy at a later stage.

## 1. Introduction

The clinical sign of scoliosis is a permanent pathological, three-dimensional axial deviation of the spine [1]. Zheng et al. [2] found a prevalence of idiopathic scoliosis of 2.4% in children aged 10–16 years, with girls being more frequently and severely affected [1,3]. X-ray projection and cross-sectional images are used to differentiate congenital scoliosis from structural idiopathic scoliosis and to classify AIS depending on the pattern and localization of the curvature [1,4]. Radiographic examinations with close follow-up are indispensable for the diagnosis and treatment decisions in patients with scoliosis [5]. For diagnosis, the degree of spinal curvature must exceed a Cobb angle of 10° in coronary view [1,6,7]. To determine the Cobb angle, it is necessary to obtain a whole-spine X-ray in the standing position. The Cobb angle is considered the gold standard and reliable for determining the extent of scoliosis and is assessed using a postero-anterior radiograph [1,8,9]. The risk of an increase in scoliosis increases the younger the patient and the higher the initial Cobb angle. In adolescents, a 10–20% probability of progression of scoliosis is found with a Cobb angle < 20° and of >70% with a Cobb angle > 20°. X-ray follow-up by means of projection images or EOS is performed at intervals of 6–12 months for Cobb angles greater than 30°. A conservative observational approach is common in patients with Cobb angles ≤ 20°; between 20 and 40°, nonsurgical therapy methods are used (i.e., physiotherapy, brace therapy); and, from ≥40 to 50°, surgical procedures are considered [1,8,10]. In addition to the initial diagnostic examinations and the preoperative imaging procedures, patients with scoliosis require numerous follow-up examinations to assess the course of the disease and, if necessary, to adjust the therapy concept, i.e., conservative vs. surgical.

According to curvature progression, King and the more recent Lenke classifications divide scoliosis into five and six main types, respectively, which have an influence on surgical planning prior to surgical treatment [11,12]. In addition to the preoperative exclusion of a Chiari malformation (type II), a tethered cord, and a syrinx, patients with planned surgery should also be excluded from the diagnosis of concomitant neurofibromatosis. A decisive point for the risk assessment of a worsening of the curvature is the skeletal maturity of the patient and the length growth that can still be expected. The degree of ossification of the iliac crest apophysis according to Risser [13] and the Sanders classification of the nondominant hand are used for radiological determination of bony maturity. The follow-up examinations are regularly performed with the aid of projection radiology examinations. In case of surgery for scoliosis, further diagnostic imaging procedures are required. For surgical planning, the following aspects have so far been clarified primarily by means of CT: determination of the pedicle thickness of vertebral bodies (for screw placement); detection of osseous stability- and growth-limiting anomalies, such as hemivertebrae and congenital vertebral defect. MRI is not a mandatory standard and is only used in specific cases to detect malformations of the brainstem, myelon, and nerves. Standardized MRI as part of primary diagnostics could detect neuronal malformations as well as incidental neuronal findings at an early stage, thereby reducing the risk of perioperative surgery.

An alternative noninvasive way of recording the geometry of the back is video-raster stereography. This method offers a reliable, radiation-free alternative to conventional radiography, especially in follow-up and screening examinations [14,15,16,17,18]. In this context, normal values of upper body posture (depending on age and sex) can be used as comparative values to identify pathological deviations [19]. The benefit of a two-dimensional photography [20] or video analysis [21] is the depth information that is calculated from the projected lines onto a curvature [16,22]. High intraclass correlation coefficients and good Cronbach’s alpha values for intra- and interday reliability for all spine parameters can be achieved when the markers are placed on defined anatomical landmarks [23,24,25,26]. This applies, among other things, to sagittal evaluation parameters, i.e., kyphosis or lordosis angle [18,27]. Additionally, a good intertester reliability of 0.979 was reported [18].

In addition, it appears that children with idiopathic scoliosis (AIS) have more frequent malocclusions than their healthy peers [28,29,30]. The interaction of neurophysiological or functional anatomical factors between dental abnormalities and posture has been demonstrated in previous studies [31,32]. Lippold et al., 2003 [33] found a statistically significant higher incidence of scoliosis (21.4%) in preschool children with Angle Class II dental malocclusion. Neck posture appears to be strongly related to the sagittal and vertical structure of the face [31]. Furthermore, there seems to be a significant relationship between the sagittal position of the mandible and a kyphotic posture [34].

To date, pediatric patients with scoliosis have been diagnosed, monitored, and treated with a range of independent specialist disciplines, including pediatricians, orthopedic surgeons, neurosurgeons, and general practitioners, each employing diverse radiological approaches. This project aims to reduce radiation exposure, minimize perioperative risks, and eliminate unnecessary duplicate examinations by establishing a standardized protocol for preoperative and follow-up care through close interdisciplinary and targeted collaboration among all involved specialists. Consistent with a holistic examination approach, this initiative will also encompass the assessment of associated comorbidities and developmental disorders, such as dental and neuronal malformations.

### 1.1. Rationale

As pediatric patients are involved, the main objective is to answer as many questions as possible preoperatively in order to avoid intraoperative surprises and to use alternative examination methods without additional (X-ray) radiation for follow-up examinations. In this context, we will investigate whether questions that could previously be answered through routine preoperative CT could also be answered by reconstructing thin-slice MRI sequences. In addition to the detection of spinal malformations by MRI in our study population, a comparison with the current literature will be conducted. We will also evaluate whether three-dimensional back scanning using light projections is suitable as an intermediate diagnostic procedure. For this purpose, the anatomical landmarks required for the back scan will remain marked during the X-ray and MRI measurements, so that the surface optometry readings obtained can be compared with the other evaluations. In addition, the influence of the examination position (supine in CT and MRI) as well as the deviation from the X-ray and back scanner standing images will be investigated. Furthermore, X-rays are taken preoperatively and, if necessary, according to the surgeon’s assessment, an EOS and a radiographic whole-spine image from the side and from the front are taken simultaneously. These are usually inadequately captured with routine cross-sectional images in patients with scoliosis. In addition to spinal changes, patients with scoliosis are more likely than patients without scoliosis to show concomitant temporomandibular pathology with jaw malalignments. To date, it is unclear to what extent these two pathologies are conditional; correlations have already been demonstrated but not causality. For the detection of temporomandibular malocclusions or the type of malocclusion, an intraoral scanner is used, with which an orthodontic model analysis can be carried out fundamentally in a very short time without any aids (such as plaster casts), without the need for further radiographs [28,29,35].

### 1.2. Study Questions

(1)Can MRI examination with additional thin-slice 3D reconstruction answer all relevant questions for preoperative planning instead of CT? Are EOS or whole spine X-ray examinations in combination with MRI data sufficient for the evaluation of the pedicles and spinal deformity?(2)Does the Cobb angle in the radiograph correlate with the calculations from the back scanner image and can follow-up checks be replaced by this video-raster stereography measurement (radiation-free)?(3)Are there any correlations between dental anomalies (e.g., crossbite) and scoliosis?

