## 2. Materials and Methods

### 2.1. Study Design and Setting

This will be a prospective, nonrandomized trial with patients with scoliosis. All subjects with severe scoliosis will be recruited from the outpatient clinic of the orthopedic department of the University Hospital Frankfurt. In addition to routine projection radiographs and preoperative CT scans that are available in some cases and/or X-ray EOS scans, special 3D thin-slice MRI sequences will be retrospectively reformatted during the required preoperative MRI scan for all study participants, as well as a three-dimensional back scan and an intraoral scan. All procedures and scoliosis parameters obtained will be compared and correlated.

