Within the framework of the project, at least 50 male and female children and adolescents aged > 7 to 18 years will be analyzed (according to the calculated power analysis). All of them will present to the Orthopaedic Clinic of the University Hospital Frankfurt with a clinical picture of scoliosis between 2022 and 2025. Height and weight will be recorded at admission. In addition, a separate medical history form will be used to record any previous conservative therapies (orthotics, braces, physiotherapy), including the type and duration of treatment. The following criteria apply for inclusion in this study:-Children/adolescents diagnosed with severe scoliosis by major curve in the X-ray > 40° [36];-Planned MRI examination of the spine at the Institute of Neuroradiology;-An EOS and/or a CT examination of the spine has already been performed as part of the diagnosis or must still be planned independent of the present project;-Children must be able to cooperate (>7 years, no motor or cognitive impairment);-Consent of the legal guardians as well as of the child.-The following criteria apply for exclusion from this study:-There will be no upper curve limit as an exclusion criterion;-Previous spinal surgery;-Mental and/or physical impairments that do not warrant a 30 min MRI scan or contraindications to an MRI scan (i.e., implants, pregnancy).

Informed consent from a parent and/or legal guardian for study participation will be obtained.

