## 3. Results

Thin-slice 3D MRI examination with reconstruction can answer all relevant questions for preoperative planning instead of CT. EOS or X-ray examination in combination with MRI data is sufficient for imaging pedicles and spinal deformity.

We expect to be able to replace preoperative CT diagnostics and obtain further information by incorporating an additional 3D MRI sequence. We anticipate that through this method, using MRI in combination with X-ray or EOS data, we will be able to detect and assess both preoperative and diagnostic parameters in a single examination. This includes parameters such as pedicle thickness according to Wanatabe, degree of disc degeneration, intraspinal anomalies, as well as formation and segmentation disorders of the vertebral bodies. Our goal is to completely eliminate the need for preoperative CT examinations by relying solely on MRI.

2.The Cobb angle in the radiograph correlates with the calculations from the back scanner image, and follow-up checks can be replaced by a three-dimensional back measurement (radiation-free).

The parameters obtained from the back scanner regarding the sagittal profile of the spine have already been validated in the general population [19]. In the context of our study, we expect a correlation between the data from the back scanner and the data from EOS and X-ray imaging, enabling the evaluation of the coronal plane and the Cobb angle in patients with severe scoliosis.

3.Correlations between dental anomalies (e.g., crossbite) and scoliosis can be proven [31,32,33,34].

We expect to find existing correlations between upper body posture and bite position, particularly in patients with severe scoliosis.

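### Every participant has severe scoliosis, so question 3 can be answered only for associations within severe scoliosis, not for an association between dental anomalies and scoliosis itself

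*Protocol article*

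**What the plan says.** - **The question.** Section 1.2, question 3 (the fourth question in the abstract): "Are there any correlations between dental anomalies (e.g., crossbite) and scoliosis".
- **The expected answer.** Section 3: "Correlations between dental anomalies (e.g., crossbite) and scoliosis can be proven". The sentence beneath it is narrower: "We expect to find existing correlations between upper body posture and bite position, particularly in patients with severe scoliosis".
- **Who is studied.** Section 2.1: "This will be a prospective, nonrandomized trial with patients with scoliosis", and "All subjects with severe scoliosis will be recruited from the outpatient clinic of the orthopedic department". Section 2.2 sets the threshold in degrees: "Children/adolescents diagnosed with severe scoliosis by major curve in the X-ray > 40". It adds: "There will be no upper curve limit as an exclusion criterion".
- **The background given.** Section 1 cites more frequent malocclusion in children with idiopathic scoliosis than in healthy children, and a raised incidence of scoliosis in preschool children with Angle Class II malocclusion. Section 1.1 contrasts patients with and without scoliosis.
- **The use foreseen.** The abstract says, conditionally, that early orthodontic treatment might help if correlations or causal links exist.
- **The number.** Section 2.2 plans at least 50 patients and expects enough power for the secondary correlations of quantitative measures. It gives no calculation for question 3.

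**The concern.** A correlation with scoliosis needs scoliosis to vary among the people studied. Here it is a condition of entry. The background in sections 1 and 1.1 consists mainly of comparisons of affected with unaffected children, so a reader will naturally take question 3 to be that comparison, and will take the expected result in section 3 as a promise to demonstrate it.

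What is at stake is the conclusion the trial may draw. If a correlation between, say, overjet and Cobb angle is found within this cohort and presented under the present wording of question 3, it will read as evidence that malocclusion goes with having scoliosis. That is the premise on which the abstract's remark about early orthodontic treatment depends, and a cohort selected at more than 40° cannot supply it.

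**Working it through.** The article gives no figure for question 3, so there is none to reproduce. The 30 patients in section 2.2 belong to the MRI-versus-CT kappa and do not enter here.

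**1. Is the association with scoliosis estimable?**
Inputs: all participants have a major curve above 40° (section 2.2); one cohort (section 2.1).
Code scoliosis as x = 1 for every patient and a dental anomaly as y = 0 or 1.
- Correlation: r = cov(x, y) / (SD(x) × SD(y)). With x constant, cov(x, y) = 0 and SD(x) = 0, so r = 0/0, which is undefined.
- Odds ratio: (a × d) / (b × c), where c and d count unaffected children with and without the anomaly. Both are 0, so this is also 0/0.

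Neither result depends on n.

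**2. Is there a comparator elsewhere in the article?**
- The literature comparison in section 1.1 concerns spinal malformations seen on MRI.
- The normative values in section 4 and under Limitations concern upper body posture.
- The Cobb range of 20–100° in Table 1 does not bring in mild cases. Entry is decided by the major curve, and lower values can be secondary curves.

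No dental reference is named.

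**3. What can the cohort estimate?**
Severity, curve direction, curve pattern and posture all vary within the cohort, and there is no upper curve limit. Associations of these with malocclusion are estimable. For two quantitative measures, by Fisher's z with n = 50 and two-sided alpha of 5%:
- |r| detectable = tanh((1.960 + z_power) / √(n − 3)), with √47 = 6.856.
- 80% power: tanh((1.960 + 0.842) / 6.856) = tanh(0.409) = 0.39.
- 90% power: tanh((1.960 + 1.282) / 6.856) = tanh(0.473) = 0.44.

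These values do not apply directly to categorical pairs such as crossbite side against curve side.

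**4. What precision does a prevalence have?**
As an illustration, assume 15 of 50 patients have a given anomaly. The article gives no such figure. The Wilson 95% interval is (0.300 + 0.0384) / 1.0768 ± 1.960 × √(0.0042 + 0.000384) / 1.0768 = 0.314 ± 0.123, or about 19% to 44%.

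**5. Does the 40° floor weaken correlations with severity?**
If selection reduces the SD of severity to a fraction u of its unrestricted value, then r′ = r × u / √(1 − r² + r²u²). The article does not give u. Taking a true r of 0.4 and n = 50, as an assumption:

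| u | r′ | Power |
|---|---|---|
| 1.0 | 0.40 | 83% |
| 0.7 | 0.29 | 54% |
| 0.5 | 0.21 | 32% |

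This shows only how strongly the answer depends on an unknown spread.

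**The case against.** The strongest reply is that the estimable reading is already in the article. Section 2.1 plans to correlate all scoliosis parameters, directly after listing the intraoral scan. The text under the expected result in section 3 speaks of posture and bite position. Section 5 plans correlations between anomalies of the temporomandibular system and of the spine. The confident wording in section 3 restates each study question as a positive statement, in a paper without data, and is a hypothesis in poor style rather than a success criterion. The abstract's remark on orthodontic treatment is conditional, section 1.1 separates correlation from causality, and section 4 says the bite data serve neither lower radiation nor safer surgery.

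Most of this stands, and it limits the point to the wording of question 3 and of its expected result. It does not remove the point: those are the statements a reader will hold the trial to, and the affected-versus-unaffected background steers them to the reading that cannot be estimated.

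Four stronger inferences are tempting, and the article does not support them:
- **That the dental data are useless or a control group is required.** Within-cohort associations remain estimable without one.
- **That the absence of dental rows from Table 1 and from the variable list in section 2.3 is an error.** Those lists mainly serve comparisons between measurement methods, and the dental measures are defined in section 2.2. Which test goes with which variable can be left to a fuller document.
- **That the investigators will present a bare prevalence as evidence of a link.** Nothing in the article says so.
- **That the 40° floor costs a known amount of power.** The size of any loss rests on a spread that is not given.

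**Conclusion.** The point holds in a limited form. As worded, and read against its own background, question 3 claims an association with scoliosis that this design cannot estimate at any sample size. This follows from the entry criteria and needs no numerical assumption. The within-cohort question can be answered, with 80% power at n = 50 for a true |r| of about 0.39 or more; that figure assumes two quantitative measures, all 50 patients evaluable, and a two-sided 5% test. Any further loss from the 40° floor cannot be sized from the article.

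The issue concerns one secondary question. The primary MRI-versus-CT kappa objective, its sample size and the data collection are untouched. It should be fixed because it changes what the trial may conclude, but it does not threaten the trial.

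**What to change.** 1. Reword question 3 in section 1.2, and the matching question in the abstract, along these lines: within patients with severe scoliosis, are malocclusion type and side associated with Cobb angle, curve direction or pattern, and back-scan posture?
2. Replace the matching statement in section 3 with an expectation limited to that cohort, and drop the claim of proof.
3. State that the prevalence of dental anomalies will be reported descriptively with a confidence interval.
4. Add one sentence, for example under Limitations: this cohort alone allows no inference about malocclusion as a marker or cause of scoliosis, or about early orthodontic intervention.

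The cost is a change of wording and a narrower claim. No additional patients, examinations or control group are needed for the narrower question. If the broader question is to be kept, an unaffected comparison group or a prespecified external dental reference would have to be added.
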